### Ethics Approval

This study has been reviewed for ethical compliance by the Queen’s University Health Sciences and Affiliated Teaching Hospitals Research Ethics Board (File Number 6028658) in March 2020. Participant data is only accessible to the health care professionals; otherwise, participants will only be identified by their study ID, and all records will be stored on a secure platform. As part of the consent process, participants are informed that they can withdraw from the study at any time and request for their data to be removed from the analysis. The research team will safeguard the data and privacy of the participants to the extent permitted by the applicable laws and duty to report.

OPTT is compliant with the Health Insurance Portability and Accountability Act, Personal Information Protection and Electronic Documents Act, and Service Organization Control-2. Also, to assure provincial and federal privacy and security regulations are met, all servers and databases are hosted in the Amazon Web Service Canada cloud infrastructure. OPTT only collects anonymized metadata used in service quality analysis; no identifiable personal information or IP addresses are collected.

### Data Analysis

Initially, all data will be examined for missing, nonsensical, and outlying variables. Missing data will be treated as missing and not imputed (ie, will be analyzed on a per-protocol basis). However, an intention-to-treat analysis will be conducted to determine the clinical effects of the e-CBT program on participants who dropped out. Based on previous experience with CBT and e-CBT in similar patient populations, the anticipated dropout rate is up to 30% by the end of the treatment or TAU phases [14,33,35,37,40]. Given the likelihood of participant dropout or withdrawal, the study sample has been purposely oversampled to obtain meaningful and statistically significant results at the end of the study. Considering the effect size for e-CBT reported by Todd et al [19] for the reduction of depression symptomatology (effect size=0.44), a significance of P<.05 and a power of 0.80, a sample size of 170 (85 per arm) would be sufficient to detect significant changes from this intervention [14,19,33,35,40,41]. As this is the first study aiming to establish an e-CBT program specific for BD-II, this sample size calculation relies on data from e-CBT specific for BD (all types). It takes into account the established effectiveness of web-based psychotherapy [14].

A 2-tailed significance level of α=.05 will be used for all calculations, except when a Bonferroni correction is needed. Possible differences between program completers and noncompleters will be determined by comparing the respective demographic information using independent sample *t* tests. A 2-by-3 repeated measures ANOVA of the primary (BD symptomatology: MADRS and YMRS) and secondary (Q-LES-Q-SF and RS-14) outcomes will be conducted to compare the effects of e-CBT + TAU to TAU only throughout the 13-week treatment course (0-, 6-, and 13-week assessment points). Variables associated with outcome measures will be determined using linear regression (continuous outcomes) and binomial regression analysis (categorical outcomes). The data collected from the posttreatment survey will be analyzed qualitatively with 2 reviewers to identify common themes and specific areas for improvement. All statistical analyses will be conducted using SPSS Statistics for Mac, version 28 (IBM Corp).

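### The default analysis is an unimputed per-protocol one, and intention-to-treat is misdescribed as an analysis of dropouts, so the plan does not say that its main conclusion rests on the randomised comparison

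*Protocol article*

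**What the plan says.** All of the following stands in the Data Analysis section of the protocol article unless another section is named.

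- Missing data and analysis set: "Missing data will be treated as missing and not imputed (ie, will be analyzed on a per-protocol basis".
- Intention-to-treat: "However, an intention-to-treat analysis will be conducted to determine the clinical effects of the e-CBT program on participants who dropped out".
- Expected loss: "the anticipated dropout rate is up to 30% by the end of the treatment or TAU phases".
- Outcome model: "A 2-by-3 repeated measures ANOVA of the primary (BD symptomatology: MADRS and YMRS) and secondary (Q-LES-Q-SF and RS-14) outcomes will be conducted", with assessments at weeks 0, 6 and 13.
- Completers and noncompleters are to be compared on demographic information only.
- The Discussion answers the expected dropout by oversampling, which it says preserves power. It does not mention bias.

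No section says whether the per-protocol or the intention-to-treat result carries the primary conclusion.

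**The concern.** Three things are run together. Leaving missing values unimputed is a way of handling missing data. Per-protocol is a choice of who is analysed. Intention-to-treat means that everyone randomised is compared in the assigned arm; it is not an analysis of effects in people who left. An analyst who follows the text literally would report a completer comparison by default and add something about dropouts.

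The randomised comparison is what protects the trial's conclusion, and completers are selected after randomisation. The selection could plausibly differ by arm:

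- The e-CBT arm can tire of 13 weekly modules with homework.
- Under Procedures, controls are offered the program after completing 13 weeks, which is a reason to stay that the e-CBT arm lacks.
- The questionnaires run on the same platform as the modules, so people who leave the modules may also stop answering. This last point is inference.

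If dropout relates to outcome differently in the two arms, the completer contrast is biased, and no increase in sample size removes that.

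**Working it through.** **1. The plan's own figure.** Inputs are "effect size=0.44), a significance of P<.05 and a power of 0.80" and "A 2-tailed significance level of α=.05 will be used for all calculations, except when a Bonferroni correction is needed", reading 0.44 as a standardised mean difference (an assumption).

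- Per arm: n = 2(1.960 + 0.842)² / 0.44² = 81.1, so 82. The t-test version gives 82.05, so 83 per arm (166 in total).
- With 85 per arm, power is 0.82 (t-test 0.81).

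So the claim that "a sample size of 170 (85 per arm) would be sufficient to detect significant changes from this intervention" reproduces, but as a number *analysed*, with almost no loss.

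**2. Who is left under the default.**

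- 0.30 × 170 = 51 lost; 170 − 51 = 119 remain, or 59.5 per arm if loss is equal.
- Power at 0.44 is then 0.67 (t-test 0.66).
- Keeping 0.80 in a completer analysis would need 82 / 0.70 = 117.1, so 118 per arm (236 in total).

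The oversampling therefore does not cover a 30% loss even for power.

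**3. Bias of the completer contrast.** In one arm, let a share d drop out, with outcomes s SD worse than completers. If the completer mean benefit is C, the whole-arm mean is (1 − d)C + d(C − s) = C − ds. Completers overstate the arm by ds, so the contrast (1 = e-CBT + TAU, 0 = TAU) is biased by

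bias = d₁s₁ − d₀s₀.

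The documents give only d up to 0.30. The s values, and a lower d₀, are assumptions.

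| d₁ | s₁ | d₀ | s₀ | Bias (SD, + favours e-CBT) |
|---|---|---|---|---|
| 0.30 | 0.5 | 0.30 | 0.5 | 0 |
| 0.30 | 0.5 | 0.30 | 0.25 | 0.075 |
| 0.30 | 0.5 | 0.15 | 0.5 | 0.075 |
| 0.30 | 0.5 | 0.30 | 0 | 0.15 |
| 0.30 | 0 | 0.30 | 0.5 | −0.15 |

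0.15 / 0.44 = 0.34, about a third of the planned effect.

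**4. Effect on false positives.** This was simulated with no true effect, 85 per arm and 30% loss in both arms. Loss follows a logistic model in the change to week 6, with the slopes shown. Assumed correlations are 0.6 (weeks 0–6), 0.7 (6–13) and 0.4 (0–13).

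| e-CBT slope | TAU slope | Completer bias (SD) | Rejection at 5% |
|---|---|---|---|
| 1 | random loss | 0.18 favouring e-CBT | 16% |
| 0.5 | random loss | 0.10 favouring e-CBT | 7.4% |
| 0.25 | random loss | 0.06 favouring e-CBT | 6.0% |
| 1 | 0.5 | 0.08 favouring e-CBT | 7.5% |
| equal | equal | about 0 | 5.1% |
| 0.5 | 1 | 0.08 against e-CBT | not reported |

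In the first scenario, a regression estimate that used the week-6 scores of dropouts had no bias. That is by construction: loss depended only on observed scores, and every dropout had a week-6 score.

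**The case against.** A reader might infer that no analysis will cover all 170 and that up to 30% of participants are thrown away. The text does not support that. An intention-to-treat analysis of some kind is promised, and Results commits to CONSORT reporting. The clause about dropouts can be read as the reason for running it, so that dropouts count. They leave the default analysis, not necessarily every analysis, and 30% is an upper limit.

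A reader might also infer that the protocol names per-protocol as its main analysis and prescribes deletion of incomplete cases. It says neither. The first follows from its being stated first and without condition, with intention-to-treat added after it. The second is the usual behaviour of repeated measures ANOVA without imputation.

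Thirdly, one might infer that the result will be biased towards e-CBT. The protocol gives a single dropout figure for both arms and nothing on mechanism, so neither size nor direction is known.

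Finally, the choice of a mixed model and of sensitivity analyses is commonly left to an analysis plan, and their absence from an article is no finding. That is right, but the point does not rest on absence. The article states a default analysis set and describes intention-to-treat wrongly, and a later plan would have to contradict that wording to put it right.

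**Conclusion.** The point holds as a defect in a stated rule. The section conflates non-imputation with per-protocol, makes that the default, misdescribes intention-to-treat, and leaves open which analysis decides. Followed as written, the default comparison is of completers.

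That much rests on the text and is firm. The size of the harm is not. Across the assumed inputs the completer bias runs from 0.15 SD in favour of e-CBT, through zero when both arms lose people in the same way, to the same amount against it. The 16% false-positive rate belongs to one fairly strong scenario of outcome-driven loss in e-CBT only and should not be quoted without it. The planned comparison of completers and noncompleters on demographics cannot show which case applies.

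**What to change.** - State that the primary analysis compares all randomised participants in their assigned arm, however many modules they completed.
- Fit a likelihood-based mixed model for repeated measures, available in SPSS, with baseline, week-6 and week-13 scores all as outcomes. A model restricted to people with a post-baseline score would not be an analysis of everyone randomised. People lost before week 6 would contribute only their baseline score.
- Except data withdrawn at a participant's request, which the Ethics Approval section allows. A full 170 cannot be guaranteed.
- Reword the intention-to-treat sentence accordingly. It should not be deleted, because it is the protocol's only intention-to-treat commitment.
- Separate the missing-data sentence from the per-protocol label, define the per-protocol set, and call that analysis supportive.
- State that the scheduled week-6 and week-13 questionnaires continue for people who stop the modules. Outcome Evaluation schedules them without such a limit, so this only makes the intention explicit.
- Optionally, add a delta-adjusted sensitivity analysis, because the mixed model relies on data being missing at random.

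The cost is wording and at most some reminders to people who have stopped; no visits or arms change. The small downside is that the estimated effect may look smaller than the completer estimate.

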Though this study has some potential limitations that mainly stem from the web-based mode of delivery of this program, the main limiting factor is that participants would need a reliable internet connection and sufficient technology literacy to participate. In turn, this could introduce biases in participant demographic characteristics. To account for this, this study will analyze demographic factors through multiple sample *t* tests to identify the impact of these factors on treatment outcomes. Additionally, the design of this study is limited by the lack of therapist and client blinding. However, due to the delivery mode and design of the program, it is not possible to conceal client allocation. Furthermore, web-based psychotherapy is often characterized by significant dropout rates, with some studies reporting a dropout rate of up to 30% by the end of the treatment or TAU phases [14,33,35,37,40]. Hence, this study is intentionally oversampling to account for this potential high dropout rate without compromising the statistical power of this study.

In conclusion, this study recognizes the significant potential of web-based psychotherapy as a tool that can lower costs and increase capacity and accessibility in mental health care, as well as the lack of available web-based psychotherapy options for individuals with BD-II. Therefore, the results of this study aim to fill an important gap in the literature through the development, implementation, and validation of a novel e-CBT program for the management of BD-II with residual depressive symptoms. Additionally, these results aim to inform clinical practice and health care policy to support the widespread implementation of web-based psychotherapy, with potential benefits to the care capacity and performance of the health care system.

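### On the stated inputs, 85 per arm is essentially the sample size without a dropout allowance, so the claim that oversampling protects power against up to 30% dropout is not supported

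*Protocol article*

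**What the plan says.** The sample size paragraph under Data Analysis takes a published effect "for the reduction of depression symptomatology (effect size=0.44") at P<.05, and concludes that with "a power of 0.80, a sample size of 170 (85 per arm) would be sufficient to detect significant changes from this intervention". The next paragraph fixes the sidedness: "A 2-tailed significance level of α=.05 will be used for all calculations, except when a Bonferroni correction is needed".

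On attrition, the same section says that "the anticipated dropout rate is up to 30% by the end of the treatment or TAU phases" and that "the study sample has been purposely oversampled to obtain meaningful and statistically significant results at the end of the study". The limitations part of the Discussion goes further and says that "this study is intentionally oversampling to account for this potential high dropout rate without compromising the statistical power of this study".

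Missing values are not to be imputed, and the analysis is described as per protocol. An intention-to-treat analysis is also announced. The planned comparison of the arms is a 2-by-3 repeated measures ANOVA over weeks 0, 6 and 13. The article gives no sample size before inflation, no inflation step, no named test for the calculation and no within-person correlation.

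**The concern.** A sample that allows for 30% loss should be visibly larger than the number needed for analysis. Here the enrolled number is almost the same as the number that the stated effect, alpha and power require with complete data. If so, the article gives inputs, a result and an assurance about dropout that do not fit together.

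At stake is the sample size justification for the primary comparison. The assurance appears twice, and the Discussion version says outright that power is kept under the dropout named. If power is appreciably below 80% at that dropout, the article understates the chance of missing an effect of the size it was planned on.

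**Working it through.** **Inputs, all from Data Analysis:** effect size 0.44, read as Cohen's d (difference divided by SD) because the text says only that it is an effect size; alpha .05, 2-tailed; power 0.80; 85 per arm, 1:1; dropout up to 30%; no imputation.

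**Step 1. Reproduce the plan's figure.** For two means, the normal approximation is

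n per arm = 2 × (1.960 + 0.842)² / d² = 2 × 7.849 / 0.1936 = 81.1, so 82.

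The noncentral t solution is 82.05, so 83. This is 164 to 166 in total, against 170 planned. By the t test, power at 85 per arm is 0.814. So 170 reproduces as the number with no dropout inflation.

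**Step 2. Allowance left.**
- Against 83 per arm: 1 − 83/85 = 2.4%.
- Against 82 per arm: 1 − 82/85 = 3.5%.

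**Step 3. What a 30% allowance would look like.** 82/0.7 = 117.1 and 83/0.7 = 118.6, so 118 to 119 per arm. Multiplying by 1.3, which under-corrects, gives 82 × 1.3 = 106.6 and 83 × 1.3 = 107.9, so 107 to 108. Neither gives 85. This only shows that 85 contains no such step.

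**Step 4. Power by dropout** (two-sample t test among completers, d = 0.44, 2-tailed .05):

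| Dropout | Completers per arm | Power |
|---|---|---|
| 0% | 85 | 0.814 |
| 5% | 80.75 | 0.794 |
| 10% | 76.5 | 0.772 |
| 20% | 68 | 0.721 |
| 30% | 59.5 | 0.663 |

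Taking 59 or 60 whole participants at 30% loss gives 0.659 or 0.667.

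**Step 5. Detectable effect.** With 59.5 per arm, 80% power is reached at d = 0.518, about 0.52 against the planned 0.44.

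**Step 6. Sensitivity to the analysis.** The correlation r between baseline and week 13 is an assumption, as the article gives none. At 59.5 per arm, with 0.44 on the scale of the outcome SD:
- Baseline-adjusted comparison, effective d = 0.44/√(1 − r²). At r = 0.3, 0.5 and 0.6, d is 0.461, 0.508 and 0.550, and power is 0.704, 0.785 and 0.845. Power reaches 0.80 at about r = 0.53.
- Change from baseline, effective d = 0.44/√(2(1 − r)). At the same r, d is 0.372, 0.440 and 0.492, and power is 0.521, 0.663 and 0.758.

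**The case against.** **The calculation may not have been a two-sample t test.** This is the strongest defence. The article names no test for the sample size, does not say what kind of effect size 0.44 is, and plans a repeated measures analysis. An efficient use of the baseline could hold 80% power at 30% loss if the correlation were about 0.53 or higher. This stands as far as it goes, and it is why a reader who concluded that the oversampling statements are simply false would go too far. But the gain cannot be credited from effect size, alpha and power alone, and a change-score contrast could equally give less than 66%.

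**30% is a ceiling.** Correct: the text says up to 30%. A reader might infer that the trial will have 66% power, but that is the figure at the plan's own upper limit, not a forecast. The defence does not rescue the statements, since the Discussion claims that power is kept at this limit, and on the two-sample reading power is below 80% once loss passes about 3.5%.

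**An intention-to-treat analysis is also planned.** Correct, so 59.5 per arm applies to an analysis of completers and not necessarily to every analysis. The article does not say how dropouts enter it, and a fuller plan may.

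**The sample does exceed the bare requirement.** It does, by 4 to 6 participants in total, which is far from an allowance for 30%.

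**A one-sided origin.** A reader might notice that a one-sided calculation (65 per arm) times 1.3 gives 84.5, and infer that the planners tested one-sided and inflated wrongly. The article describes no such step and states a 2-tailed alpha, so this is conjecture and no part of the point.

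**Conclusion.** The inconsistency holds. On the stated inputs, 85 per arm is the number for about 80% power with essentially complete data. Its margin for loss is about 2% to 3.5%, against an anticipated loss of up to 30%. The statements in Data Analysis and the Discussion that the sample is oversampled for this dropout, with power intact, are not supported by those inputs. For a two-sample comparison of completers at the upper limit of dropout, the type II error is about 34% (1 − 0.66) where the plan implies 20%.

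This rests on three assumptions: 0.44 is Cohen's d, the comparison is between two groups at one time point, and dropouts contribute nothing to it.

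**What to change.** 1. In Data Analysis, restate power for d = 0.44 across the dropout range: about 81% with no loss, 79% at 5%, 77% at 10%, 72% at 20% and 66% at 30%. Add that the effect detectable with 80% power at 30% loss is about 0.52. Name the test and the type of effect size on which the figures rest.
2. Delete or correct both oversampling sentences, the one in Data Analysis and the one in the limitations part of the Discussion.

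These two changes are wording only and need no added enrolment. Their cost is a less favourable stated power.

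3. Optional: if a gain from baseline adjustment is to be claimed, plan a baseline-adjusted week-13 comparison explicitly and show power over a range of assumed correlations. At 59.5 per arm it is about 70% at r = 0.3, 78% at r = 0.5 and 84% at r = 0.6. This changes the planned analysis, so it should be decided and recorded as such; a single assumed correlation would not be enough.

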## Methods

### Participants

This is the protocol for a randomized controlled trial studying the efficacy of a novel e-CBT program. Participants (N=170) diagnosed with BD-II experiencing residual depressive symptoms will be recruited from the Mood and Anxiety Clinic at Providence Care Hospital, Kingston Health Sciences Center, family physicians, other health care professionals, and self-referrals within Ontario, Canada. Additionally, recruitment efforts will be carried out through flyers in social gathering areas (eg, coffee shops, college campuses), media advertisements, and expert end user referrals. After providing consent to participate in the study, the participants will complete a Mini International Neuropsychiatric Interview 7.0.2 (MINI) with a trained research assistant [30]. The MINI assesses 17 common psychiatric conditions following the diagnostic criteria of the Diagnostic and Statistical Manual of Mental Disorders, 5th edition (DSM-5) [30]. Inclusion criteria include being 18 years or older at the start of the study, a diagnosis of BD-II based on the MINI assessment, a Montgomery-Åsberg Depressive Rating Scale (MADRS) score of mild to moderate depression symptomatology (MADRS score 7-34), competence to consent and participate, ability to speak and read English, and consistent and reliable access to the internet [14,31-33]. Exclusion criteria include acute hypomanic or manic episodes, acute psychosis, severe alcohol or substance use disorder, and active suicidal or homicidal ideation. Additionally, individuals who are currently receiving or have received CBT in the past 6 months will be ineligible to avoid confounding treatment effects.

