### Procedures

Eligible participants will be randomly assigned to either a 13-week e-CBT program in addition to TAU (n=85; e-CBT + TAU group) or TAU only (control group; n=85). If interested, participants in the control group will be offered access to the e-CBT program after completing 13 weeks as part of the control group. The e-CBT program will be delivered as an augmentation to TAU through the Online Psychotherapy Tool (OPTT), a secure and interactive platform developed by the principal investigator (PI) [14,34]. TAU will consist of medications, regular physician or clinician visits, referrals, or consultations that are conducted outside of this research study.

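### The planned 2-by-3 ANOVA treats baseline as an outcome and tests change without direction; a baseline-adjusted week-13 contrast would answer the end-of-treatment question, usually with more power

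*Protocol article*

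**What the plan says.** The between-arm analysis is given in the protocol article, Methods, Data Analysis: "A 2-by-3 repeated measures ANOVA of the primary (BD symptomatology: MADRS and YMRS) and secondary (Q-LES-Q-SF and RS-14) outcomes will be conducted". It compares the arms "throughout the 13-week treatment course (0-, 6-, and 13-week assessment points"), so the week-0 score is one of the three repeated outcomes. The section does not say which term of the ANOVA decides. Regression is mentioned only for finding variables associated with outcome, not for comparing the arms.

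The sample size stands in the same section. Its inputs are an effect for the "reduction of depression symptomatology (effect size=0.44") and "a significance of P<.05 and a power of 0.80", and it concludes that "a sample size of 170 (85 per arm) would be sufficient to detect significant changes from this intervention". No test, time point, within-person correlation or repeated-measures structure is given with that figure. On error control the section says "A 2-tailed significance level of α=.05 will be used for all calculations, except when a Bonferroni correction is needed". The Outcome Evaluation section defines the primary outcome as change in symptoms, compared between arms, and names no primary time point.

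**The concern.** In a randomised trial the expected arm difference at week 0 is zero. Using week 0 as an outcome level spends a measurement that could have reduced residual variance. The question of whether the arms change differently then falls to the arm-by-time interaction, which asks only whether the three arm differences are unequal. It does not ask in which direction, or whether a benefit is still there when treatment ends.

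Two things are at stake. A significant result would not by itself show an end-of-treatment benefit. And the planned test may have less power than the 80% on which the sample size rests, although the baseline data that would recover power are collected anyway.

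**Working it through.** **Inputs from the protocol article.** Effect size 0.44, two-sided alpha 0.05, power 0.80 and 85 per arm (Data Analysis; arm sizes also in Procedures). Three time levels: 0, 6 and 13 weeks.

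**Assumptions, not in the document.** The 0.44 is a standardised arm difference at week 13. SDs are equal at all visits and data are complete. The correlation between visits is equal (compound symmetry), ρ = 0.3, 0.5 or 0.7. The week-6 difference is either half (0.22) or all (0.44) of the week-13 difference.

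**1. The plan's own figure.** For a two-sample comparison, n per arm = 2(1.960 + 0.842)² / 0.44² = 15.70 / 0.1936 = 81.1, so 82. With the noncentral t distribution it is 83 per arm, 166 in total, within 3% of 170. At 85 per arm the t test has 81% power. So 170 looks like a single two-group comparison. That is inferred from reproducing the figure; the document names no test.

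**2. Arm-by-time interaction.** λ = (n/2) × Σ(δⱼ − δ̄)² / (1 − ρ), on 2 and 336 df.
- Differences (0, 0.22, 0.44): the sum of squares is 0.0968 and 42.5 × 0.0968 = 4.114. Dividing by 1 − ρ gives λ = 5.88 / 8.23 / 13.71.
- Differences (0, 0.44, 0.44): the sum of squares is 0.1291 and 42.5 × 0.1291 = 5.485. This gives λ = 7.84 / 10.97 / 18.28.

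**3. Baseline-adjusted week-13 contrast.** λ = (n/2) × 0.44² / (1 − ρ²), on 1 df. Since 42.5 × 0.1936 = 8.228, λ = 9.04 / 10.97 / 16.13.

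**4. Power with 85 per arm.**

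| Test | ρ = 0.3 | ρ = 0.5 | ρ = 0.7 |
|---|---|---|---|
| Interaction, half effect at week 6 | 57% | 73% | 92% |
| Interaction, full effect at week 6 | 70% | 85% | 97.5% |
| Baseline-adjusted week 13 | 85% | 91% | 98% |

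The interaction loses 28 / 18 / 6 points in the half-effect case and 14 / 6 / 0.4 points in the full-effect case. At ρ = 0.5 with a full week-6 effect both tests have λ = 10.97, so the 6-point gap there comes entirely from spending 2 df instead of 1.

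**5. Direction.** Differences of (0, 0.44, 0), a benefit gone by week 13, also have a sum of squares of 0.1291. Under equal correlations the interaction therefore has the same power for that pattern as for (0, 0.44, 0.44): 85% for both at ρ = 0.5.

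**6. Other correlation patterns.** By simulation with the Greenhouse-Geisser correction under AR(1), 85 per arm and a full week-6 effect, interaction against adjusted contrast is about 91% against 90% at adjacent correlation 0.7, and 98% against 96% at 0.8. With half the effect at week 6 and adjacent correlation 0.7, the adjusted contrast leads, 91% against 79%. Under equal correlations of 0.8 with a full week-6 effect the two are level (99.8% against 99.7%).

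**The case against.** The strongest reply is that the ANOVA is a valid test and that the size of the loss depends on two inputs the document does not give. That stands. The interaction reaches 80% from a correlation of about 0.6 with half the effect at week 6, or about 0.45 to 0.5 with the full effect, and in some patterns it matches or slightly beats the adjusted contrast. A reader might infer that the trial is underpowered because of this choice; the documents do not support that as a general statement.

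A reader might also infer that the analysis contradicts the sample-size calculation. It does not do so explicitly: the 0.44 is given without metric, time point or test, so the mismatch is a reasonable inference only.

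Nor does the document support resting the case on the arm main effect, which would average in the null week-0 difference. An outcome worded as change points to the interaction. The eligibility window ("MADRS score 7-34") likewise does not show that baseline is strongly prognostic. It gives no correlation, and restricting range tends to lower one.

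Finally, a week-0-to-13 change contrast can be drawn from the same ANOVA, and the Bonferroni clause is compatible with follow-up contrasts. This is correct, and such a contrast would have direction. But its variance factor, 2(1 − ρ), exceeds 1 − ρ² for every ρ below 1. Its power is 67 / 81 / 96% at ρ = 0.3 / 0.5 / 0.7, still below 85 / 91 / 98%.

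**Conclusion.** The point holds as one of efficiency and targeting, not validity. Three features do not depend on the assumed correlation: week 0 is an outcome level, the natural test of change has 2 df and no direction, and the stated N of 170 carries no repeated-measures input. On the assumptions listed, the cost against a baseline-adjusted week-13 contrast ranges from about 28 percentage points of power to nil, with a slight reversal possible under AR(1) correlation when the full effect is present early. Because the article states the method, this is a choice to reconsider and not a detail left to a fuller document. It should be changed before the data are analysed.

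**What to change.** Replace the ANOVA with a mixed model for repeated measures. The outcomes are the week-6 and week-13 scores. The fixed effects are arm, visit, arm-by-visit, baseline score and baseline-by-visit, with unstructured covariance. Name the week-13 arm difference (1 df, with its 95% CI) as the primary test, and use the same model for the Q-LES-Q-SF and RS-14. State in the sample-size paragraph which test and time point the 0.44 refers to.

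The cost is a change of wording. No extra participants or visits are needed, and the named software has the procedure. The model also keeps week-6 data from people who later drop out, whom a standard repeated measures ANOVA would exclude. There is one small downside: the primary question narrows from the course over 13 weeks to the difference at end of treatment. Report the week-6 difference from the same model as supportive.
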